# Exercise therapy, manual therapy, or both, for osteoarthritis of the hip or knee: a factorial randomised controlled trial protocol

**DOI:** 10.1186/1745-6215-10-11

**Published:** 2009-02-08

## Abstract

**Background:**

Non-pharmacological, non-surgical interventions are recommended as the first line of treatment for osteoarthritis (OA) of the hip and knee. There is evidence that exercise therapy is effective for reducing pain and improving function in patients with knee OA, some evidence that exercise therapy is effective for hip OA, and early indications that manual therapy may be efficacious for hip and knee OA. There is little evidence as to which approach is more effective, if benefits endure, or if providing these therapies is cost-effective for the management of this disorder. The MOA Trial (Management of OsteoArthritis) aims to test the effectiveness of two physiotherapy interventions for improving disability and pain in adults with hip or knee OA in New Zealand. Specifically, our primary objectives are to investigate whether:

1. Exercise therapy versus no exercise therapy improves disability at 12 months;

2. Manual physiotherapy versus no manual therapy improves disability at 12 months;

3. Providing physiotherapy programmes in addition to usual care is more cost-effective than usual care alone in the management of osteoarthritis at 24 months.

**Methods:**

This is a 2 × 2 factorial randomised controlled trial. We plan to recruit 224 participants with hip or knee OA. Eligible participants will be randomly allocated to receive either: (a) a supervised multi-modal exercise therapy programme; (b) an individualised manual therapy programme; (c) both exercise therapy and manual therapy; or, (d) no trial physiotherapy. All participants will continue to receive usual medical care. The outcome assessors, orthopaedic surgeons, general medical practitioners, and statistician will be blind to group allocation until the statistical analysis is completed. The trial is funded by Health Research Council of New Zealand Project Grants (Project numbers 07/199, 07/200).

**Discussion:**

The MOA Trial will be the first to investigate the effectiveness and cost-effectiveness of providing physiotherapy programmes of this kind, for the management of pain and disability in adults with hip or knee OA.

**Trial registration:**

Australian New Zealand Clinical Trials Registry ref: ACTRN12608000130369.

## Background

Non-pharmacological, non-surgical interventions, such as the treatments offered by physiotherapists, are recommended as the first line of treatment for hip and knee osteoarthritis (OA) [1-3], however there is still insufficient evidence about many such interventions to make specific recommendations regarding management of this disorder [4,5]. Given the prevalence of OA, its economic and human burden, and accumulating evidence supporting the effectiveness of various physiotherapy interventions for patients with OA of the hip or knee, further research is warranted [5]. Two common forms of physiotherapy intervention are exercise therapy and manual therapy.

Although it is well established that various forms of exercise are effective in reducing pain and increasing physical function in people with knee OA, there is still little knowledge about which forms of exercise are most effective [4-8]. Little is known about whether effectiveness endures beyond the medium term, with few studies following up to 12 months, and none beyond 15 months [9]. Few trials have investigated the relative benefits of differing exercise approaches: systematic reviews of exercise therapy for the osteoarthritic knee have included randomised controlled trials, which are clinically diverse, with variability in the interventions employed [4,7,9,10]. However, one meta-analysis of trials on strengthening exercises concludes that, to get the maximum benefit of strengthening exercises, it is necessary to also include range-of-motion and stretching exercises in a multi-modal approach [11]. There are no trials that we know of investigating a supervised, individualised, multi-modal programme of exercise therapy for OA of the knee, although clinicians consider this to characterise the 'ideal standard of clinical practice' [12].

Regarding OA of the hip, there have been very few randomised controlled trials of exercise therapy, however what data there are indicate the benefits may be similar to those found for knee OA [5,11,13-15]. Although there are no systematic reviews available specific to exercise therapies for hip OA, reviews that have summarised either hip and/or knee OA identified no trials of strengthening exercises or of land-based supervised exercise for people with OA of hip and had not undergone hip joint replacement surgery [8,9,11,12,15]. Two more recent trials in the literature indicate that a programme of multimodal exercise training and lifestyle advice [14] and a multi-modal strengthening, stretching, gait training and range of motion exercise programme [16] may be effective for reducing pain and improving function in patients with hip OA, however effect sizes were small in both trials. Again, little is known about whether effectiveness endures beyond the medium term.

New developments in manual physiotherapy have demonstrated very promising improvements in pain and physical function [16-19], but effectiveness has not yet been definitively established [5]. There is one clinical trial in the literature of manual physiotherapy for hip OA: compared with exercise physiotherapy, manual physiotherapy resulted in superior improvements in pain and physical function, that endured to six months follow-up [16]. Deyle and colleagues have conducted two trials of manual physiotherapy for knee OA [17,18]. In the first, a multi-modal intervention of individually tailored manual therapy plus stretching, strengthening, range of motion and home exercises resulted in clinically significant superior outcomes compared with a placebo control group [18]. In the second, the multi-modal intervention of individually tailored manual therapy plus stretching, strengthening, range of motion and home exercises resulted in clinically significant superior outcomes compared with home exercises alone [17]. In both studies, benefits were still evident at the 12-month follow-up.

Our project is an extension of these recent studies [16-18], and is designed to answer questions that have not been addressed in the literature to date. None of the three previous controlled trials of manual physiotherapy has directly compared manual therapy interventions with usual care. We have identified no trials directly comparing an individually tailored, supervised multi-modal exercise therapy programme with usual care, or to individually tailored manual therapy. No trials have investigated if there is a synergistic, antagonistic or neutral effect when both exercise and manual therapy are employed. Few of the previous trials have assessed the effectiveness of their interventions beyond a short to medium term. The MOA Trial responds to the dearth of economic analysis studies in this field, and will report cost-utility over a 24-month timeframe.

The MOA Trial will investigate the long-term effectiveness and cost-effectiveness of both a multi-modal, individualised, supervised exercise therapy programme, and an individualised manual therapy programme, for the management of pain and disability in adults with hip or knee OA. This publication outlines the design and analysis plan for the MOA Trial.

### Specific aims

The specific aims of this trial are to establish if:

1. Exercise therapy versus no exercise therapy improves disability at 12 months in adults with hip or knee OA.

2. Manual therapy versus no manual therapy improves disability at 12 months in adults with hip or knee OA.

3. Provision of physiotherapy programmes in addition to usual care to adults with hip or knee OA is more cost-effective than usual care alone at 24 months.

In addition, we will test for differences in the secondary outcomes at 9 weeks, 6 months, and 12 months, and for an interaction between the interventions for disability at 12 months. The secondary outcomes include physical performance tests, patients' global assessment, and joint replacement surgery (Table 1).

**Table 1 T1:** Outcome measures

Primary Outcome measure*	Data collection instrument
WOMAC composite score	WOMAC-3.1 patient-rated questionnaire [30-32]

**Secondary Outcome measures**	

Timed up-and-go	Physical test [38,39]
30 second sit-to-stand	Physical test [37]
40 m self-paced walk	Physical test [32,39]
WOMAC subscales: A) Pain; B) Stiffness C) Physical Function;	WOMAC-3.1 [33,34] patient-rated questionnaire
Numeric pain rating	NPRS [33,34] patient-rated questionnaire
Self-efficacy and pain beliefs	The Pain Belief Screening Instrument [40,41]
Depression	The two-item case-finding instrument [42]
Patient's global assessment	GROC [33,34,36] patient-rated scale
OARSI response criteria	Composite of WOMAC, NPRS, GROC [34]
American College of Rheumatology criteria for diagnosis of OA	Clinician-rated criteria [22-24,45,46] from physical tests and symptoms
New Zealand National Clinical Priority System score	Clinician-rated criteria [47];
Adverse events	MOA field team audit; ODHB records; self-report questionnaire
Overall health status^†^	SF-12 general health survey [43]
Surgical intervention^†^	Self-report questionnaire; health system records [44]
Healthcare consumption and related costs^†^	Self-report questionnaire; health system records

*The primary end-point for data analysis is 12 months. All outcome measures will be undertaken at baseline, 9 weeks, 6 months, 1 year and 2 years, with the exception of patients' global assessment and OARSI response criteria, which will not be assessed at baseline. ^†^The primary endpoint for cost-utility and surgical intervention is at 2 years. WOMAC = Western Ontario and McMaster osteoarthritis index; NPRS = numeric pain rating scale; GROC = global rating of change; OA = Osteoarthritis; OARSI = Osteoarthritis Research Society International; MOA = the Management of OsteoArthritis Trial; ODHB = Otago District Health Board.

## Trial design and methods

This project is a 2 × 2 factorial randomised controlled trial (Figure 1). We have chosen a factorial design because it is an efficient way to evaluate more than one intervention in a single trial [20,21]. This is because all participants are included in each of the primary analyses, whereas in a trial of, say, three parallel arms evaluating two different interventions compared with a control arm, only two thirds of participants are used for each comparison. However, the sample size benefits gains of this design only occur when the assumption of no interaction between the two interventions is met. We do not anticipate any interaction effects since these are uncommon [21], even in drug trials [20]. However, we will report an estimate of the interaction effect as is recommended for all factorial trials [20] (see Data Analysis, below).

**Figure 1 F1:**
[figure not shown]
**2 × 2 factorial trial design**. Note: All groups receive usual medical care.

### Participants

We will recruit 224 participants through two sources: a) patients attending general practitioners (GPs) with hip or knee OA; and b) patients attending the Department of Orthopaedic Surgery (Outpatient Clinic, Dunedin Hospital, New Zealand) for an orthopaedic consultation for consideration of hip or knee joint replacement surgery.

To be eligible, participants must meet clinical criteria for diagnosis of OA of the hip or knee according to American College of Rheumatology criteria [22-24].

Exclusion criteria will include:

• previous knee or hip joint replacement surgery of the affected joint;

• any other surgical procedure of the lower limbs in the previous 6 months;

• rheumatoid arthritis;

• initiation of opioid analgesia or cortico-steroid or analgesic injection intervention for hip or knee pain within the previous 30 days;

• uncontrolled hypertension or moderate to high risk for cardiac complications during exercise [25];

• physical impairments unrelated to the hip or knee preventing safe participation in exercise, manual therapy, walking or stationary cycling, such as: vision problems that affect mobility, body weight greater than 155 kg, neurogenic disorder, primary or significantly limiting back pain, advanced osteoporosis, or inability to walk 10 metres without an assistive device;

• inability to comprehend and complete study assessments or comply with study instructions;

• stated inability to attend or complete the proposed course of intervention and follow-up schedule.

Figure 2 shows a diagram illustrating the expected flow of participants through recruitment, assessment and intervention. A research nurse will identify potential participants at the Dunedin Hospital Orthopaedic Clinic point of entry. The research nurse will initially screen each potential participant against the inclusion and exclusion criteria by chart review and questioning by telephone. We will keep a screening log, recording the criteria eliminating all those found to be ineligible. Willing potential participants will be given an appointment at the Centre for Physiotherapy Research, where researchers will obtain informed consent and baseline measures.

**Figure 2 F2:**
[figure not shown]
**Diagram of participant flow**. OA = osteoarthritis; RN = Research Nurse; CRA = Clinical Research Administrator; MT = manual physiotherapy; Ex = exercise physiotherapy; GP = general medical practitioner.

Researchers at the Centre for Physiotherapy Research will evaluate each potential participant against the inclusion and exclusion criteria by clinical history, physical examination and review of self-report questionnaires. Participants will then be randomised (refer to randomisation and allocation concealment, below).

In the event of recruitment numbers falling behind targets, we will seek ethical approval to recruit people with hip or knee OA by advertising in the community. Previous research indicates there may be no clinically or statistically significant differences in most important baseline measures or mean effects of treatment between patients referred by GPs for clinical consultation versus people recruited from the community via newspaper advertisements [26].

#### Randomisation and allocation concealment

Participants will be randomised using TENALEA, which is an online, central randomisation service, currently in deployment phase with a grant from the e-TEN programme of the European Union (LSHC-CT-510736). This Trans-European Network for Clinical Trial Service provides a secure randomisation service over the internet. The TENALEA service will generate and hold the randomisation schedule. Allocation concealment will be ensured, as the service will not release the randomisation code until the patient has been recruited into the trial, which takes place after all baseline measurements have been completed.

Randomisation will be stratified by condition (hip or knee). Within each stratum, participants will be randomised to one of the four intervention groups using block allocation. The block size will be subject to random variation.

#### Blinding

Outcome assessors will be blind to group allocation, and will not be involved in providing the interventions. The orthopaedic surgeons and GPs managing the participants' care will be blind to group allocation; physiotherapists delivering the intervention cannot. The participants will be informed they are in a "physiotherapy" or the "usual care" group, and the type of physiotherapy intervention (manual, exercise, or both) will not be specified. The statisticians conducting the statistical analyses will be blind to group allocation until the analyses are completed.

### Interventions

Protocols for the physiotherapy interventions will be described in a Manual of Standard Operating Procedures (MSOP), available from the principal investigator ([name]). Guidelines for individual tailoring of activity prescription and progression will be described within these protocols. Secondarily, additional interventions will be individually tailored as needed, according to the results of a standardised physical examination that will include tests and measures to assess impairments in physical function (e.g. muscle strength, muscle length, joint range of motion). Impairments revealed will be matched explicitly to interventions, described in the MSOP, intended to directly address each impaired physical function. In this manner, the plan of care for each patient is individually tailored from a standardised menu of interventions, using a defined algorithm, in the categories of 'exercise therapy' and 'manual therapy' (described below). Individualised home exercise instructions, plus compliance logs, will also be provided. The methodology will therefore be consistent with the 'ideal standard of clinical practice' [12] and the research designs of previous studies [16-18].

Participants randomised to receive trial physiotherapy will receive nine treatment sessions: seven in the initial nine weeks of the trial and two 'booster' sessions at week 16. Given the chronic, progressive nature of the disease, we will recommend participants return to receive additional 'booster' doses of two sessions every four months, as is recommended by current best evidence, previous investigators and expert opinion [9,17,27,28].

#### Usual care

The control group will receive no trial physiotherapy. All participants will continue to receive the usual, normal routine care offered by their own GP and other healthcare providers. In this way, this trial evaluates the effectiveness of physiotherapy care *in addition to *usual medical care.

We will send a letter to each participant's GP informing her or him that the patient is participating in the trial, but will not reveal which group the patient is in and will request that the GP not ask. We will also request that the GP contact the researchers before adding physiotherapy to the patient's plan of care during the trial. The researchers will discourage contamination of the 'usual care only' group by referral to physiotherapy within the 9-week intervention phase, however it would be unethical and unreasonable to recommend physiotherapy be withheld from the 'usual care only' group throughout the follow-up period of the trial. We will measure potential contamination with non-trial physiotherapy by participant self-report questionnaire.

All participants will continue to receive their usual care at the Dunedin Hospital Orthopaedic Clinic, by consultant orthopaedic surgeons blind to group allocation. Participation in the trial will not affect patients' prioritisation for, or access to, joint replacement surgery.

#### Exercise physiotherapy

The exercise therapy protocol will primarily consist of a multi-modal, supervised programme of warm-up/aerobic, muscle strengthening, muscle stretching, and neuromuscular control exercises. Secondarily, additional exercise therapy interventions will be prescribed individually for each participant on the basis of the physical examination findings, from a limited list of interventions defined in the MSOP. These will be informed by evidence-based best practice [5,9-13,16-18,29]. The protocol does not allow therapist-applied manual forces. Participants will be instructed in an individualised home exercise programme of warm-up/aerobic, muscle strengthening, muscle stretching, and neuromuscular control exercises as detailed in the MSOP.

#### Manual physiotherapy

The manual therapy protocol will consist primarily of procedures intended to modify the quality and range of motion of the target joint and associated soft tissue structures. Secondarily, additional manual therapy interventions will be prescribed individually for each participant randomised to this intervention on the basis of the physical examination findings, from a limited list of interventions. These will be informed by evidence-based best practice [16-19]. For our purposes, we define manual therapy as the application of therapist-applied manual forces in procedures intended to modify the quality and range of motion of the target joint and soft tissue structures. The protocol does not allow muscle strengthening or neuromuscular control exercises. Participants will be instructed in an individualised home exercise programme of joint range of motion exercises.

#### Combination therapy

This protocol will consist of a combination of both exercise therapy and manual therapy interventions, as described above.

### Outcome measures

#### Primary

The primary outcome will be disability at one-year follow-up using the WOMAC (Western Ontario and McMaster osteoarthritis index). The WOMAC is a widely used, reliable, valid and responsive measure of outcome in people with osteoarthritis of the hip or knee [30-32].

#### Secondary

We will also include the outcome measures recommended by OMERACT-OARSI guidelines [33,34]. These require measures of pain, physical function and patient global assessment. We will assess pain using the WOMAC pain sub-scale and numeric pain rating scale [35]; physical function using the WOMAC physical function sub-scale; and patient global assessment using a 15-point global rating of change [36] (Table 1). We will also assess change in physical performance tests: the timed up-and-go, 30-second sit-to-stand, and 40 metre self-paced walk tests [32,37-39] and psychological function [40-42]. We will assess overall health status using the SF-12 (Quality Metric, Inc., Lincoln, Rhode Island, USA) [43], and will measure health care consumption costs, including surgical interventions, by records audit and patient self-report questionnaire [44]. We will track and classify adverse events. We will continue to assess the American College of Rheumatology criteria for the diagnosis of OA of the hip or knee [22-24,45,46]; the New Zealand National Clinical Priority System score [47] (where available); and exercise compliance.

#### Follow-up

A summary of the follow-up schedule is shown in Table 1. Assessments will be performed by researchers at baseline, 9 weeks, 6 months, 1 year, 2 years and, if future funding permits, subsequent years.

### Sample size

The primary endpoint in this trial is disability at 12 months, measured using the numeric rating scale version of the WOMAC scale. We calculated the sample size to detect a difference of 28 points for each of the main effects, namely, exercise therapy versus no exercise therapy, and manual therapy versus no manual therapy. We regard this as the minimum clinically important difference between groups in patients with moderate OA [17,18,32,48-50]. Assuming a standard deviation of 50 points [17,18], and a type I error rate of 5%; a sample of 45 participants per intervention group (90 per row (Figure 1)) will be sufficient to detect the differences with approximately 95% power. With a sample of this size, the predicted width of the 95% confidence interval for each intervention effect will be approximately ± 14.6 points [51]. Allowing for 20% attrition, we plan to recruit 56 participants per group, providing a total of 224 participants.

Using the assumptions above, a sample of this size will have limited power of approximately 46% to detect an interaction between exercise therapy and manual physiotherapy. However, these calculations may be conservative since we have not incorporated the stratification variable, or correlation between baseline and follow-up measures, due to lack of prior information.

### Data analysis

#### Analyses subsets

The primary analysis of the data will be undertaken using the principle of intention-to-treat (ITT) [45]. Our ITT analysis will include all participants, including those who are not fully compliant and those with missing outcome data. While we plan to implement procedures to minimise loss to follow-up and patient withdrawal, we expect to observe some attrition. We plan to employ multiple imputation to handle missing data in the analysis. Multiple imputation, compared to other case deletion strategies, can provide valid inferences with less restrictive assumptions surrounding the mechanism for missing data [52-54].

As part of the secondary analyses, we plan to undertake two per-protocol analyses for the primary outcome (WOMAC composite score) at 12 months. The first analysis will include participants who did *not *have hip or knee replacement surgery. The second analysis will include participants who complied with the intervention protocol; where compliance will be defined as attendance of 80% of scheduled intervention visits, 60% of prescribed home exercise sessions in the intervention groups, and low contamination (less than 4 physiotherapy visits) in the comparison group.

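### The compliance-based per-protocol analysis limits outside physiotherapy only in usual care and filters on adherence only in the other three arms, which does not fit the factorial contrasts

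*Protocol article*

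**What the plan says.** Under Data analysis, Analyses subsets, the protocol article makes intention-to-treat primary and adds two per-protocol analyses of WOMAC at 12 months. For the second, "compliance will be defined as attendance of 80% of scheduled intervention visits", followed by "60% of prescribed home exercise sessions in the intervention groups, and low contamination (less than 4 physiotherapy visits) in the comparison group".

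The contrasts are fixed elsewhere. The first aim is whether "Exercise therapy versus no exercise therapy improves disability at 12 months in adults with hip or knee OA", the second is its counterpart for manual therapy, and the Sample size section powers the trial for "exercise therapy versus no exercise therapy, and manual therapy versus no manual therapy".

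The Usual care section shows what contamination means. It is non-trial physiotherapy, self-reported by questionnaire, and the stated worry is about the arm with no trial physiotherapy. Referral of that arm is discouraged during the nine-week intervention phase and not beyond it.

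Home exercise is prescribed in the manual arm too: "Participants will be instructed in an individualised home exercise programme of joint range of motion exercises". The home-session criterion therefore applies in all three physiotherapy arms.

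On visits, the Interventions section says "Participants randomised to receive trial physiotherapy will receive nine treatment sessions: seven in the initial nine weeks of the trial and two 'booster' sessions", and then "we will recommend participants return to receive additional 'booster' doses of two sessions every four months".

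**The concern.** The rule contrasts several intervention groups with one comparison group. The analysis contrasts two margins, and on each margin the comparison side is half usual care and half a single-therapy arm. Two problems follow.

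- **Contamination.** For the exercise contrast, the contamination that matters includes outside exercise therapy in the manual-only arm, and the reverse holds for the manual contrast. The rule sets no limit on either. Such participants stay in as compliant comparators and pull the estimated effect towards zero.
- **Selection.** Three arms are cut down to participants who attend and do their home exercises, while usual care has no adherence filter. If adherers tend to do better whatever they receive, the retained groups are no longer comparable and the estimate leans towards benefit.

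At stake is a pre-specified secondary analysis of the primary outcome at the primary time point. Readers may take it as the effect in those who were treated as intended.

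**Working it through.** **Inputs from the protocol article (Sample size).** Difference 28, SD 50, two-sided 5%, 45 evaluable per arm, 90 per margin.

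**The plan's own figures.** SE = 50 × √(2/90) = 7.45. Power = Φ(28/7.45 − 1.96) = 0.964, against a stated figure of approximately 95%. Half-width = 1.96 × 7.45 = 14.6, as stated. The sample size is not in question. The article gives no figure for the per-protocol set, so the rates below are assumptions.

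**Weights in the factorial estimate.** Let a be the fraction of each physiotherapy arm that passes the filter, with usual care kept whole. In the additive two-factor model the exercise effect is an inverse-variance average of two differences:

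- exercise-only minus usual care, with weight 2/(3 + a);
- combination minus manual-only, with weight (1 + a)/(3 + a).

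Both weights are 0.5 when a = 1. When a = 0.6 they are 0.556 and 0.444.

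**Step 1: dilution.** Suppose a fraction c of the manual-only arm obtains exercise therapy outside the trial at its full effect of 28. With equal arms the exercise effect falls by 28 × c × 0.5:

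| c (assumed) | fall | exercise effect |
|---|---|---|
| 10% | 1.4 | 26.6 |
| 20% | 2.8 | 25.2 |
| 30% | 4.2 | 23.8 |

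At a = 0.6 the weight is 0.444, and the range for 10% to 30% is 26.8 to 24.3.

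**Step 2: selection on adherence, with no true effect.** Suppose adherers do better than non-adherers by d points regardless of treatment. Keeping only adherers shifts each physiotherapy arm by s = (1 − a) × d. The shift cancels in combination minus manual-only but not in exercise-only minus usual care, so each main effect is biased by 2s/(3 + a).

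- a = 0.9, d = 10: s = 1, bias = 2/3.9 = 0.5.
- a = 0.6, d = 30: s = 12, bias = 24/3.6 = 6.7.

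If an interaction were fitted in this set, the whole of s would enter it, so 1 to 12 points of apparent antagonism.

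**Step 3: the same bias in terms of a correlation.** Keep the top 60% of a normally distributed adherence trait. Its mean there is 0.644 SD. With SD 50 and correlations of 0.2 to 0.4 between adherence and a better WOMAC, the arm-level shift is 0.644 × 50 × 0.2 = 6.4 to 0.644 × 50 × 0.4 = 12.9. Multiplied by 2/3.6, that is 3.6 to 7.2 per main effect.

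**Step 4: scale.** At a = 0.6 the main-effect SE is 50/√(45 × 0.6/1.6 + 45 × 0.6/2) = 9.1. A bias of 7.2 is about 0.8 SE and about a quarter of 28.

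**Step 5: attendance cut-off.** 80% of nine visits is 7.2, so at least 8. If later boosters counted as scheduled and brought the total to 11 or 13 by 12 months, the cut-off would be 9 (from 8.8) or 11 (from 10.4). The article does not date the later boosters, so these totals are inferred.

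**The case against.** The strongest objections, and what stands of each:

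- **Any per-protocol analysis selects on adherence, and usual care has no programme to adhere to.** True. The article makes intention-to-treat primary and rests no conclusion on this set. That limits the importance of the point. It does not make the retained groups comparable.
- **The sizes are assumed.** This stands. The Secondary analyses section carries over the primary model's covariates, among them baseline pain, mental health and self-efficacy. The differences and correlations above must therefore be what remains after adjustment. The figure relevant to this trial is the one per main effect, not the larger one per arm.
- **Crossover may be rare.** The article asks every participant's general practitioner to contact the researchers before adding physiotherapy. This reduces contamination but does not bring it into the compliance definition.
- **A complier-average estimate has weaknesses of its own.** It needs a definition of therapy received. It also assumes that allocation acts only through that therapy, which is open to doubt when participants know whether they are in a physiotherapy or a usual-care group and rate the outcome themselves. This is why it should be added and not substituted.

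Two stronger readings are tempting. A reader might infer that the visit limit covers the whole no-exercise or no-manual side, so that every compliant single-therapy participant, with at least 8 trial visits, is excluded. The Usual care section does not support this: contamination there is non-trial physiotherapy, discussed for the usual-care-only group, and the rule's singular comparison group fits that meaning. A reader might also infer that the Interventions section gives two conflicting session counts. It gives nine sessions and then recommends further ones, which calls for a clarification and is not a contradiction.

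**Conclusion.** The point holds in limited form. On the likelier reading, the rule leaves non-trial physiotherapy unlimited in the single-therapy arms, although those arms make up half of each comparison side. It also filters on adherence in three arms out of four.

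The first defect dilutes a 28-point effect to about 26.6 to 23.8, if 10% to 30% of the single-therapy arm crosses over at full effect. The second biases each main effect towards benefit by about 0.5 to 7 points, if 60% to 90% pass the filter and adherence keeps the assumed association with outcome after adjustment. The two act in opposite directions, but nothing makes them cancel. The article supplies none of these rates.

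The primary analysis, the sample size and the stated power are not affected. What is affected is how far this secondary result can be trusted as the effect of therapy received.

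**What to change.** 1. In Analyses subsets, state that the limit of fewer than four visits counts non-trial physiotherapy only, and apply it in all four arms.
2. Report the result as supportive and as selected on adherence.
3. Add a complier-average estimate on all randomised participants: two-stage least squares with exercise therapy received and manual therapy received as exposures, the two randomised factors as instruments, and the primary-model covariates. State the exclusion-restriction assumption and define therapy received beforehand.
4. State whether the recommended booster sessions count as scheduled visits for the 80% criterion.

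The cost is a few sentences and one extra model. It would draw on attendance and on the non-trial physiotherapy that the article already plans to collect by questionnaire. The article does not say whether that questionnaire records the type of therapy, which the added model would need. The complier-average interval will be wider, and applying the limit in every arm may remove some further participants from the per-protocol set. All of this should be settled before the analysts are unblinded.
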